### 1.2 Purpose of the analyses

The aim of the SCOPE study is to determine the effectiveness and safety of introducing a revised case management package to facilitate well-tolerated and effective radical cure of patients with vivax malaria at 10 public health care facilities in Indonesia and Papua New Guinea.

The revised case management package has been prioritised and endorsed by the respective Ministries of Health and will include: 1) semi-quantitative point-of-care glucose-6-phosphate dehydrogenase (G6PD) activity assessment prior to treatment with primaquine, 2) prescription of high dose (7mg/kg body weight total) primaquine over 7 (**PQ7**), 14 (**PQ14**) days or 8 weeks (**PQ8W**), to all eligible patients presenting with *P. vivax* malaria, 3) patient education and counselling prior to treatment and supervision of the first dose of primaquine at the health care facility, 4) community-based clinical review at day 3 of primaquine treatment to encourage treatment adherence and facilitate detection and management of adverse events to treatment and 5) improved malariometric surveillance and pharmacovigilance.

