**Exploratory endpoints:**

|        |                                                                                                                                         |
|--------|-----------------------------------------------------------------------------------------------------------------------------------------|
| S1.EE1 | Maximum absolute fall in haemoglobin within the first 7 days                                                                            |
| S1.EE2 | Maximum proportional fall in haemoglobin within the first 7 days                                                                        |
| S1.EE3 | Reduction of >25% in haemoglobin to a concentration of < 7 g/dl                                                                         |
| S1.EE4 | POST HOC : Level of agreement between SD Biosensor and HemoCue for haemoglobin measurement at study clinics and in the community |
| S1.EE5 | POST HOC : Methaemoglobin concentrations on days 3 and 7                                                                         |

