### 3.1.2. Stage 2 – Large-scale implementation and feasibility study

Stage 2 of the study will be a feasibility study conducted at 10 community health-care facilities: 6 sites in Indonesia and 4 sites in Papua New Guinea. The primary purpose of Stage 2 is to determine the feasibility and cost-effectiveness of the complete revised case management initially studied in Stage 1. Robust Pre-Implementation malarimetric surveillance for a minimum of 12 months along with quantitative surveys of baseline operational metrics and costs will be followed by coordinated introduction of the revised case management across all study health facilities and a minimum of a further 12 months of surveillance – creating an interrupted time series comparing the endpoints listed in section 2.2.2.

During Stage 2 study procedures will be the same as those for Stage 1, except that the procedures will be performed by routine healthcare staff. All patients will be reviewed by community health workers (CHW) at home 3 days after starting PQ. The review may also take place at the health facility, if the patient presents there. Exceptionally, the follow-up may also take place via a phone call if the patient is not physically reachable at home. The CHW will complete a signs and symptom checklist to detect early indicators of haemolysis or other AESI. Patients with signs of haemolysis or other AESI will have their primaquine ceased and will be referred to the health facility for medical review. Patients tolerating their medication will be encouraged to adhere to a full (7 or 14 days) course of treatment. Safety outcomes occurring between day 3 and end of treatment will be detected passively by community-based health workers, study health facilities and regional hospitals.

Continuous surveillance and pharmacovigilance over the entire study period will enable interrupted time-series analyses of malarimetric indices (see section 2.2.2).

Figure 1 presents the study schedule for the baseline data, pre-implementation stage, and stages 1 and 2.

**Figure 1. Study overview**[figure not shown]

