### 9.1. Stage 1 – Preliminary safety and feasibility study

For Stage 1, the number and proportion of patients experiencing at least one SAE (S1.PE1) or at least one AESI (S1.PE2) will be computed by treatment arm (PQ7, PQ14, PQ8w), and described in summary tables which will include breakdown by type of event, severity, relatedness to treatment, and timing of occurrence (see Appendix 4 for example Tables 1-4). The number and proportion of patients permanently discontinuing treatment (S1.SE4) will be computed by treatment arm and presented in a summary table, with breakdown of reason for discontinuation. Absolute numbers of AESIs with denominators (S1.PE1-3) and proportions with 95% confidence intervals (calculated using a binomial distribution) will be presented in tabular and graphical format. A full tabulation of all SAEs will also be presented.

For S1.EE3, the number and proportion (and 95% Confidence Interval) of patients observed to have a >25% reduction in haemoglobin to a concentration below 7 g/dl will be computed by treatment arm (PQ7, PQ14, PQ8w), and described in summary tables.

For S1.EE1 and S1.EE2, the unadjusted and adjusted mean absolute and proportional maximum change in haemoglobin within 7 days (95% CI) respectively will be presented by treatment arm (PQ7, PQ14, PQ8w). The adjusted means will be estimated from a linear regression model that adjusts for baseline haemoglobin level and G6PD enzyme activity level. The association between change in haemoglobin from baseline to day 2 and G6PD enzyme activity level will be estimated from a linear regression model that allows for a nonlinear association using fractional polynomials and adjusts for baseline haemoglobin level, age, sex and baseline parasitaemia. A scatterplot of the data will be presented with observations labelled by treatment arm (PQ7, PQ14, PQ8w).

For S1.EE4, the mean difference, standard deviation of the difference and 95% limits of agreement between Biosensor and HemoCue haemoglobin measurements will be computed using Bland-Altman plots (Bland JM & Altman DG 1995), stratified by day of measurement (day 0, 3, 7) and country. The data will be presented in tabular and graphical formats.

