| txother                       | Other Treatment                                    | Other Treatment                                                                                                     |
| comments                      | Comments                                           | Comments                                                                                                            |
| Level 2 Review CRF     |                                                    |                                                                                                                     |
| scopeid                       | N/A                                                | SCOPE Study ID                                                                                                      |
| studysite                     | N/A                                                | Study Site                                                                                                          |
| l2_reviewdat                  | N/A                                                | Date of Review                                                                                                      |
| l2_reviewday                  | N/A                                                | Day of Review                                                                                                       |
| l2_reviewdayoth               | N/A                                                | Day of Review (other)                                                                                               |
| l2_location                   | N/A                                                | Location of Assessment                                                                                              |
| l2_locationoth                | N/A                                                | Location of Assessment (Other)                                                                                      |

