| l2_dkurine         | N/A                | Dark urine                                                                     |
| l2_dkurinedat      | N/A                | Dark urine - Date of Onset                                                     |
| l2_othsymp         | N/A                | Other symptom(s)                                                               |
| l2_othsympdat      | N/A                | Other symptom(s) - Date of Onset                                               |
| g6pd               | U/g Hb             | G6PD                                                                           |
| g6pdoor            | N/A                | G6PD Out of Measuring Range                                                    |
| hb                 | g/dL               | Hb                                                                             |
| hboor              | N/A                | Hb Out of Measuring Range                                                      |
| l2_g6pdtester      | N/A                | Indonesia: Staff ID (G6PD Tester)
PNG: ID of staff conducting G6PD test     |
| l2_hbhcdat         | N/A                | Hemocue Date (today)                                                           |
| l2_hbhc            | g/dL               | Hemocue Hb (today)                                                             |
| l2_hbhcoor         | N/A                | Hemocue Hb Out of Measuring Range                                              |
| l2_chghbhc         | g/dL               | Hemocue Change in Hb (Calculated)                                              |
| l2_changehbhc      | g/dL               | Hemocue Change in Hb                                                           |
| l2_g6pddat         | N/A                | Biosensor Date (today)                                                         |
| l2_g6pd            | U/g Hb             | G6PD (today)                                                                   |
| l2_g6pdoor         | N/A                | G6PD Out of Measuring Range                                                    |
| l2_hb              | g/dL               | Hb (today)                                                                     |

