| Figure 1 | Study overview                                                                                                                                                                                                                                                                                                                                                                                                                                        |
| Figure 2 | Incidence of symptomatic P. vivax malaria episodes over time. The introduction of the implementation package at 6 months is indicated by the dashed red vertical line. The trend lines for the pre- and post-implementation stages are presented as solid blue lines, and the counterfactual to the post-implementation trend presented as a dashed blue line.
[Note: the example figure is given for a single health facility site] |
| Figure 3 | Bland–Altman plots comparing the measurements haemoglobin obtained using HemoCue and SD Biosensor.                                                                                                                                                                                                                                                                                                                                                    |

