| Intermediate Males                             |                           |                                      |
| Deficient                                      |                           |                                      |
| Unknown                                        |                           |                                      |
| Haemoglobin (median, IQR, range)        |                           |                                      |

|                        |  |  |
|------------------------|--|--|
| Anaemia <7g/dL (n (%)) |  |  |
|------------------------|--|--|

**Table 9. Estimates of the effect of the implementation package on the prevalence of *P. vivax* parasitaemia and severe anaemia (haemoglobin < 7g/dl) in patients presenting with fever in the cross-sectional surveys in the pre-implementation and post-implementation (Stage 2) phases of study**

|                                     | Pre-implementation | Post-implementation | Post- versus pre-implementation |
|-------------------------------------|--------------------|---------------------|---------------------------------|
| P. vivax parasitaemia | Est of P (lb, ub)  | Est of P (lb, ub)   | Est of PR (lb, ub)              |
| Severe anaemia               | Est of P (lb, ub)  | Est of P (lb, ub)   | Est of PR (lb, ub)              |

Est (lb, ub) = Estimate (lower bound of 95% CI, upper bound of 95% CI), P – Prevalence, IRR – Prevalence Ratio

**Table 10. Descriptive statistics and 95% limits of agreement for haemoglobin measurements obtained by using Biosensor and HemoCue, stratified by day of measurement (day 0, 3, 7) and country**

|                  | HemoCue
haemoglobin (g/dL) | SD Biosensor
haemoglobin (g/dL) | Difference between
two measurements
(g/dL) | 95% limits of
agreement
(g/dL) |
|------------------|-------------------------------|------------------------------------|--------------------------------------------------|--------------------------------------|
|                  | Mean (SD); N                  | Mean (SD); N                       | Mean (SD) [95% CI]                               |                                      |
| Indonesia |                               |                                    |                                                  |                                      |

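### S1.EE4 names two measurement settings, clinic and community, but no planned output reports device agreement by setting

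*SAP*

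**What the plan says.** SAP section 2.2.1 lists S1.EE4 among the exploratory endpoints, marked post hoc: "Level of agreement between SD Biosensor and HemoCue for haemoglobin measurement at study clinics and in the community". Section 5.1 gives the background. After some implausible Biosensor haemoglobin values early in Stage 1, readings were duplicated on HemoCue where that device was available, for patient safety and to judge how reliable the Biosensor is.

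Section 9.1 plans the mean difference, its SD and the 95% limits of agreement, "stratified by day of measurement (day 0, 3, 7) and country". Dummy Table 10 in Appendix 3 ("Descriptive statistics and 95% limits of agreement for haemoglobin measurements obtained by using Biosensor and HemoCue, stratified by day of measurement" and country) has three day rows under Indonesia and three under PNG. Figure 3 is listed in Appendix 2 as "plots comparing the measurements haemoglobin obtained using HemoCue and SD Biosensor", with no split by setting.

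The data dictionary in Appendix 1 has a field on the Level 2 Review CRF labelled "Location of Assessment" (l2_location), with a further field for other locations. The same CRF carries the follow-up Biosensor and HemoCue haemoglobin values (l2_hb, l2_hbhc). The Level 3 Review CRF has its own location field (l3_location) and both haemoglobin readings.

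**The concern.** The endpoint names two places of measurement, and the analysis uses neither as a stratum. A reader of the Stage 1 results who wants to know how the Biosensor performs outside the clinic will find no row or plot that says so.

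This is of some interest because the duplicate testing was started over doubts about the device, and conditions of use may differ between a facility and a patient's home. Stage 1 is also the main source of such pairs: the SAP revision history (v9.0) states that in Stage 2 haemoglobin is routinely collected at baseline only.

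**Working it through.** The SAP states no figure for S1.EE4, so there is none to reproduce. The check is a comparison of texts, followed by an illustration with assumed values.

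**1. Is setting covered anywhere else?** Section 9.1, the Table 10 title and rows, and the Figure 3 title do not mention it. Section 6.1 lists study site as a Stage 1 subgroup, but that is the health facility a patient belongs to, not where a reading was taken.

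**2. Can day stand in for setting?**

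- Day 0: this is the enrolment visit at the facility. The Baseline/Enrolment CRF holds both haemoglobin readings and a study site but no location-of-assessment field. The stratum is clinic-only.
- Day 3: section 1.2 describes the package as including "community-based clinical review at day 3 of primaquine treatment". Section 3.2 has Stage 1 patients attending follow-up evaluations on days 3 and 7. Section 3.1.2 describes home review and adds: "The review may also take place at the health facility, if the patient presents there". That is Stage 2 text, but the section also says that Stage 2 procedures match Stage 1 apart from who performs them.
- Day 7: section 3.1.1 requires a review by staff and does not fix the place.
- The Level 2 CRF records location for each review and allows for other locations, so location is expected to vary.

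Day therefore separates day 0 (clinic) from follow-up (clinic, community or both). Contrasting day 0 with days 3 and 7 as a substitute for setting would also compare untreated patients with patients on treatment.

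**3. What could pooling do within day 3 or day 7?** Let *w* be the share of community pairs, clinic bias 0 with SD *s₁*, and community bias *b* with SD *s₂*. Then:

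- pooled bias = *w·b*
- pooled variance = (1−*w*)*s₁*² + *w·s₂*² + *w*(1−*w*)*b*²
- limits = pooled bias ± 1.96 × pooled SD

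All values below are assumed, in g/dl, with *s₁* = 1.0. Clinic limits are therefore 0 ± 1.96 = −1.96 to 1.96 throughout.

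| *b* | *s₂* | *w* | Pooled bias | Pooled SD | Pooled limits | Community limits |
|---|---|---|---|---|---|---|
| 0 | 1.0 | any | 0 | 1.00 | −1.96 to 1.96 | −1.96 to 1.96 |
| 0.5 | 1.5 | 0.25 | 0.12 | 1.17 | −2.16 to 2.41 | −2.44 to 3.44 |
| 0.5 | 1.5 | 0.50 | 0.25 | 1.30 | −2.30 to 2.80 | −2.44 to 3.44 |
| 0.5 | 1.5 | 0.75 | 0.38 | 1.41 | −2.39 to 3.14 | −2.44 to 3.44 |
| 1.0 | 1.0 | 0.50 | 0.50 | 1.12 | −1.69 to 2.69 | −0.96 to 2.96 |
| 1.0 | 1.5 | 0.50 | 0.50 | 1.37 | −2.18 to 3.18 | −1.94 to 3.94 |

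Worked line, *b* = 1.0, *s₂* = 1.0, *w* = 0.5: variance = 0.5 + 0.5 + 0.25 = 1.25; SD = 1.118; limits = 0.5 ± 1.96 × 1.118 = −1.69 to 2.69.

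The first row shows that pooling is harmless when the two settings behave alike. The other rows show pooled limits that describe neither setting. The SAP does not say which row is closest to the truth.

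**The case against.** The endpoint wording does not ask for separate or compared results. Its mention of clinics and the community can be read as saying where the paired readings come from, and the purpose in section 5.1, assessing Biosensor reliability, is not tied to setting. On that reading, results by day and country serve the endpoint reasonably well. This stands as a fair alternative reading, so it would go too far to say that the endpoint's question goes unanswered. It does not remove the gap: the endpoint names two settings, and no output shows either one at follow-up.

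Two stronger conclusions are tempting.

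- A reader might infer that clinic and community readings are mixed throughout. The documents do not support this: day 0 is clinic-only, and mixing on days 3 and 7 in Stage 1 is an inference from the sections cited above, not something the SAP states. One setting could dominate a follow-up stratum.
- A reader might infer that pooling understates the bias where falls in haemoglobin are judged. That holds only if bias is larger in the community than at facilities on the same day, and nothing in the SAP shows that. The plan already reports days 3 and 7 apart from day 0.

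Practical limits also stand. HemoCue was used only where available, the coded values of the location fields are not shown, and duplicates began after Stage 1 had started. With about 800 patients planned, some 300 of them in PNG, some cells may be small.

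**Conclusion.** The mismatch between endpoint and analysis is real and can be read directly from sections 2.2.1 and 9.1 and Table 10: two settings are named and none is reported. It concerns days 3 and 7 only. Its effect on the results cannot be sized from the SAP, because neither the share of community pairs nor any difference in bias or SD between settings is given; it is nil if the settings behave alike. The point rests on the assumption, supported but not stated for Stage 1, that follow-up readings came from both places. S1.EE4 is post hoc and exploratory, so this is a low-priority improvement.

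**What to change.** In section 9.1, Table 10 and Figure 3, keep the planned results and add the day 3 and day 7 Bland-Altman results by location of assessment (facility or community) within country. Take the location from l2_location, or from l3_location where the pair comes from a Level 3 review, and state how other locations are classified. Keep day 0 as clinic, and give the number of pairs in every cell. Where a cell has too few pairs for usable limits of agreement, pool the countries or give the mean difference only.

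The cost is small and needs no new data collection. The six day-by-country rows (2 × 3) become ten cells by setting (2 countries × [1 for day 0 + 2 for day 3 + 2 for day 7]), which is four more. The downside is less precise limits in the smaller cells.

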### 9.2. Stage 2 – Large-scale implementation and feasibility study

For Stage 2, the proportion of eligible patients receiving all elements of the implementation package correctly, and other related outcomes, will be presented for all patients, as well as stratified by study country and health facility. Corresponding 95% confidence intervals of these outcomes will be calculated assuming a binomial distribution.

The change in the incidence of symptomatic *P. vivax* malaria episodes (S2.SE15 - effectiveness endpoint) between the pre-Implementation Stage and post-implementation stage (Stage 2) will be shown graphically using an interrupted time series graph. Following the recommendations of Turner et al. (2020) the following components will be displayed: the health facility site-level (aggregated) data points versus time point of measurement (e.g. monthly for primary outcome) as a scatter plot; the interruption time will be displayed with a vertical dashed line; and the pre-interruption and post-

interruption trend lines; and the counterfactual trend line (an example is given in Appendix 3, Figure 2).

The estimate of the effect of the implementation package will be determined by fitting a segmented regression model to the monthly health facility level data (Bernal J.L. et al. 2017). For the segmented regression model, we will estimate the impact of the revised case management as:

- a) a level change comparing six months post-implementation to pre-implementation stage (Figure 2).
- b) the difference in trends before and after introduction of the implementation package (i.e. slope change comparing post-implementation to pre-implementation stage) (Bernal J.L. et al. 2017) (Figure 2).

A binary indicator variable will take the value of 1 for all time points following the start of the stage 2 implementation package within each health facility site, and a value of 0 for all other timepoints. Health facilities also participating in stage 1 will have this data excluded from analysis as seen in Appendix 4: Figure 1. A sensitivity analysis will be performed where the binary indicator variable takes the value of 1 for all timepoints following the start of implementation, including both stage 1 and 2.

See Appendix 4: Figure 1 for the data to be included in the pre- and post-implementation periods for S2.SE15.

The model will include time (month) as a continuous variable, a binary variable for the implementation intervention (see (a) and (b) above), an interaction between elapsed time (since implementation) and the implementation, seasonal variation in malaria (captured using splines), adjusted for potential time-varying confounding variables including large scale malaria control activities outside of the SCOPE study and unexpected antimalarial stock outages, and allowing for a random effect for intercept to account for clustering by health facility site (Turner SL et al. 2021).

For the effectiveness outcome S2.SE15, monthly incidence of symptomatic *P. vivax* malaria will be calculated using clinic catchment populations provided by health facilities (or if not available, the most recent census). Incidence rate ratios (IRRs) (95% CIs) for the intervention effect will be estimated from a negative binomial regression model fitted to the monthly aggregated data.

**Figure 2.** Example impact model for the implementation package on the effectiveness outcome measure S2.SE15 (incidence of symptomatic *P. vivax* malaria infections). An impact model with an immediate change in level and slope. While immediate level change is allowed to occur in this model at the time of implementation, the estimand of interest with regards to level change will be calculated 6 months after implementation (at 12 months) relative to the implementation timepoint (at 6 months).

[figure not shown]

For comparison of outcomes S2.SE16 (the proportion of febrile patients with asexual *P. vivax* parasitaemia by microscopy) and S2.SE14 (the proportion of patients with severe anaemia (haemoglobin < 7 g/dl), determined from cross-sectional surveys in the pre- and post-implementation periods), prevalence ratios (95% CIs) for the intervention effect will be estimated from log-binomial regression models, and if there are convergence issues, Poisson regression with robust variance will be performed (Barros AJD & Hirakata VN 2003).

Individual patient data on the risk of representation with vivax malaria within 6 months to the same health facility site (S2.SE17) will be analysed using survival analysis and visualised with Kaplan-Meier curves. The risk of recurrence will be determined for all patients eligible for PQ treatment and compared between the pre- and post-implementation stages. Multivariable Cox proportional hazards regression will be used to compare these same groups, controlling for age, sex, body weight, calendar time (month), seasonality (captured using splines) and shared frailty of health facility. The validity of the proportional hazards assumption will be assessed visually using Schoenfeld residuals and stratified analyses will be conducted where the assumption is violated.

For S2.EE1, the number and proportion (and 95% Confidence Interval) of patients observed to have a >25% reduction in haemoglobin to a concentration below 7 g/dl will be computed by treatment arm (PQ7, PQ14, PQ8w), and described in summary tables.

